### Objectives and hypothesis

#### Hypotheses

Primary—the glycemic control of people with pre-diabetes who are treated with Lysulin™ tablets will be better than that of the control group.Secondary—progression to diabetes would be reduced and other related metabolic parameters (serum insulin, total cholesterol, triglyceride, HDL cholesterol, LDL cholesterol and blood pressure) will be improved in the treatment group in comparison to the control group.

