#### Secondary outcomes

Change in FPG and OGTT plasma glucose from baseline.Development of diabetes during follow-up, as indicated by either FPG > 125 mg/dl and/or 2-h OGTT plasma glucose > 199 mg/dl and/or HbA1c > 6.5%, confirmed during follow-up visits [27].Change in lipid profile from baseline (total cholesterol, LDL, HDL and TAG).Change in insulin resistance from baseline. Insulin resistance would be measured by the Homeostasis Model of Assessment—Insulin Resistance (HOMA-IR) calculations based on fasting blood glucose and fasting serum insulin. Β-cell function would be evaluated in vivo (HOMA-B calculation) and in vitro.Change in anthropometric assessment such as body weight, height, body mass index (BMI), waist circumference (WC), hip circumference (HC) and waist:hip ratio (WHR) from baseline.Change in systolic blood pressure (SBP) and diastolic blood pressure (DBP) from baseline.

Level of physical activity (International Physical Activity Questionnaire (IPAQ) short form) and dietary intake (validated Food Frequency Questionnaire) would be assessed in both groups as they are confounding factors affecting glycemic control.

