### Statistical analysis

Parametric and nonparametric statistical tests will be applied using SPSS version 16 (SPSS Inc., Chicago, IL, USA) and Stata/SE 10.0 (Stata Corporation, College Station, TX, USA) for data analysis. FFQ data will be analyzed using NutriSurvey 2007 (EBISpro, Germany), nutrient analysis software for Windows, modified for Sri Lankan food items and recipes, and will be reported as the intake of calories, carbohydrates, fat, proteins and dietary fibers per day. Summary statistics will be calculated and presented as mean, standard deviation and proportion by group. The baseline and end of study characteristics as well as the laboratory findings of the groups will be compared using two-sample and paired *t* test, and *P* < 0.05 will be considered significant. The Homeostasis Model Assessment (HOMA2) calculator will be used to calculate β-cell function (HOMA-β) and insulin resistance (HOMA-IR) based on fasting insulin and plasma glucose [32]. The Homeostatic Model Assessment (HOMA) is a method used to quantify insulin resistance and β-cell function. It has good correlation with the traditional, invasive and time-consuming euglycemic clamp method (*r* = 0.88) which is used to measure insulin resistance and β-cell function.

Multiple regression analyses will be performed, where change in FPG/OGTT/HbA1c post intervention from baseline are the continuous dependent variables and independent variables will be age (continuous), treatment group (0, placebo; 1, Lysulin™), gender (0, female; 1, male), physical activity (continuous), BMI (continuous), energy intake (continuous), carbohydrate intake (continuous) and baseline FPG/OGTT/HbA1c. All analyses will follow intention-to-treat principles and a prespecified analysis plan. Where appropriate, sensitivity analyses will be conducted (e.g., control for additional covariates; and bootstrapped *P* values for skewed outcomes). In the case of missing data values, we will apply mean imputation and regression imputation where rates are low, and consider multiple imputations where they exceed 10%.

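### Secondary outcomes only: the planned baseline-adjusted regression stops at FPG, OGTT and HbA1c; extending it to lipids, insulin, HOMA, anthropometry and blood pressure would gain precision at no cost

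*Protocol article*

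**What the plan says.** In the protocol article, Secondary outcomes defines the outcomes at issue as changes: "Change in lipid profile from baseline (total cholesterol, LDL, HDL and TAG"), "Change in insulin resistance from baseline", anthropometry, and "Change in systolic blood pressure (SBP) and diastolic blood pressure (DBP) from baseline". Beta-cell function (HOMA-B) is listed alongside insulin resistance. Under Hypotheses, serum insulin, lipids and blood pressure are expected to show a between-arm effect: they "will be improved in the treatment group in comparison to the control group".

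Statistical analysis then names two kinds of test.

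- **t tests:** "The baseline and end of study characteristics as well as the laboratory findings of the groups will be compared using two-sample and paired" t tests, with significance at P < 0.05.
- **Regression:** "Multiple regression analyses will be performed, where change in FPG/OGTT/HbA1c post intervention from baseline are the continuous dependent variables". Treatment group is a covariate, and the list of covariates ends with "carbohydrate intake (continuous) and baseline FPG/OGTT/HbA1c".

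No regression is named for any other outcome.

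**The concern.** Each of these secondary outcomes has a baseline and a follow-up value, and the hypothesis compares the arms. The named tests do not combine the two well. The paired t test uses each person's baseline but only within an arm, so it cannot answer a between-arm question. The two-sample t test compares the arms, but it either leaves the baseline out (if applied to end-of-study values) or uses it only by subtraction (if applied to changes). The better model is already in the plan, but for three outcomes only.

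Precision is at stake. The sample size was set for HbA1c alone, so these outcomes have whatever power is left to them. An inefficient test can leave a real effect non-significant. Stratification is by age and gender only. A chance imbalance in baseline lipids, weight or blood pressure is therefore not controlled by design, and an unadjusted test does not correct for it.

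**Working it through.** **Inputs from the protocol article (Sample size).** Two-sided 5% (critical value 1.96), 80% power, HbA1c difference 0.5, SD 0.82, 20% drop-out, 55 per arm.

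**The plan's own figure.** N = (1/0.5 + 1/0.5) × (1.96 + 0.84)² / (0.5/0.82)² = 4 × 7.84 / 0.3718 = 84.3. That is 42.2 per arm, rounded up to 43, or 86 in total. Then 86/(1 − 0.20) = 107.5, so 108. The stated 108 is reproduced. It concerns HbA1c only; no power is stated for the outcomes discussed here.

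**Assumptions, not in the documents.** A true effect of 0.4 SD on a secondary outcome; a baseline-to-6-month correlation r, shown as a range; equal SDs at the two times. Completers per arm: 55 × 0.80 = 44.

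**Method.** Relative to the SD of a single measurement, the residual SD f is:

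- end-of-study t test: f = 1
- t test on change: f = √(2(1 − r))
- baseline-adjusted model: f = √(1 − r²)

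The noncentrality is (0.4/f) × √(44/2) = 1.876/f. Power comes from the noncentral t distribution with 86 degrees of freedom.

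| r | f, change | f, adjusted | Power, end values | Power, change | Power, adjusted |
|---|---|---|---|---|---|
| 0.3 | 1.183 | 0.954 | 45.8% | 34.8% | 49.4% |
| 0.5 | 1.000 | 0.866 | 45.8% | 45.8% | 57.2% |
| 0.7 | 0.775 | 0.714 | 45.8% | 66.8% | 73.8% |
| 0.8 | 0.632 | 0.600 | 45.8% | 83.5% | 87.1% |
| 0.9 | 0.447 | 0.436 | 45.8% | 98.6% | 98.9% |

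Loss against the adjusted model:

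- **End values:** 57.2 − 45.8 = 11 points at r = 0.5, 28 at 0.7 and 53 at 0.9.
- **Change scores:** 11 points at r = 0.5, 7 at 0.7, about 4 at 0.8 and 0.3 at 0.9.

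The variance of the adjusted estimate is (1 − r²) times that of the end-value comparison and (1 + r)/2 times that of the change comparison. For 0 < r < 1 both factors are below 1, so the direction does not depend on the reading.

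At the larger effect borrowed from the HbA1c calculation (0.5/0.82 = 0.61 SD) and r = 0.5, power is 80.7% for either t test and 90.4% adjusted, a gain of 9.7 points.

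**Chance imbalance.** Suppose there is no treatment effect and the baseline means differ by k = 2 standard errors.

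- **End values:** the test statistic is approximately normal with mean rk and variance 1 − r². The chance that it passes ±1.96 is 13%, 22% and 36% at r = 0.5, 0.7 and 0.9.
- **Change scores:** the mean is −(1 − r)k/√(2(1 − r)) and the variance (1 + r)/2. The chance is 13%, 10% and 7%.

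An imbalance of at least 2 standard errors arises in roughly 5% of randomisations for a given variable. Averaged over all randomisations, both tests hold 5%.

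**The case against.** **The t test may be on changes.** Secondary outcomes defines these measures as changes, so a two-sample test of such an outcome could well be a test of change scores, in which the baseline does enter. This stands as a fair reading. A reader might infer that the plan definitely discards the baseline in every between-arm comparison; the text does not establish that. The sentence on t tests does speak of baseline and end-of-study characteristics, so it does not establish the change reading either. If these variables track strongly within a person, change scores come close to the adjusted model and the loss is small.

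**The t test is valid.** Correct. It is unbiased under randomisation, and the raised false-positive rates hold only given an unusual imbalance. A reader who took them for the test's overall error rate would be mistaken.

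**The detail may lie elsewhere.** The section refers to a prespecified analysis plan that is not shown, and it allows sensitivity analyses with additional covariates. The plan may extend the regression. But the article is not silent here: it names a test for these outcomes and a better model for three others. The sensitivity analyses are optional and tied to no outcome, so they do not replace the named test.

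**The effect sizes are not the trial's.** True. The protocol sizes none of these outcomes, so no stated power is contradicted. The figures show the scale of the loss under stated assumptions.

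**Conclusion.** The point holds as a free improvement for secondary outcomes. For lipids, serum insulin, HOMA-IR and HOMA-B, anthropometry and blood pressure, the named between-arm test is less precise than the baseline-adjusted model already planned for FPG, OGTT and HbA1c, on either reading of what is tested. How much is lost depends on that reading and on an unknown correlation. At 44 per arm, 0.4 SD and r from 0.5 to 0.9, the loss is about 11 to 53 points of power for end-of-study values, and about 11 points falling to under 1 for changes.

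It would go too far to call these comparisons invalid or the trial's main conclusion exposed. HbA1c, the primary outcome, is in the regression with its own baseline value.

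**What to change.** In Statistical analysis, extend the regression to each of these continuous outcomes: total, LDL and HDL cholesterol, triglycerides, serum insulin, HOMA-IR, HOMA-B, weight, BMI, waist and hip circumference, waist:hip ratio, SBP and DBP. For each, regress the 6-month value (or the change) on treatment group, that outcome's own baseline value, and the stratification factors age and gender. Report the adjusted between-arm difference with its 95% CI as the result, and keep the two-sample and paired t tests as descriptive. State whether the two-sample test is applied to end-of-study values or to changes.

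The cost is a sentence or two and a few more regressions. Defining the outcomes as change from baseline already requires the baseline values, and the same type of model is already planned. No patients, visits or measurements are added, and according to Trial status enrolment has not begun.

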### Sample size

A total of 110 adults with pre-diabetes will be recruited for the study after a screening test confirming the presence of pre-diabetes as defined in ‘Population’ and further eligibility screening against other inclusion/exclusion criteria described in ‘Inclusion and exclusion criteria’. Summaries of previous studies of oral antidiabetic drugs suggest that they reduce HbA1a levels by 0.5–1.5% [22]. Numerous studies have shown that zinc supplementation reduces HbA1c by around 0.5% [15]. Hence, in the absence of preliminary studies in a comparable cohort, we assumed an HbA1c reduction of 0.5%. The number of patients required for determination of a 0.5% reduction of HbA1c in the treatment arm, in comparison with the placebo arm, at 80% power and 95% confidence interval with a drop-out rate of 20% was 108 patients. Hence, a total of 110 adults with diagnosed pre-diabetes will be recruited for the study. Subjects will be randomly and equally assigned into two groups (*n* = 55 each) and will receive either Lysulin™ oral tablet or an identical placebo daily for a period of 6 months. The formula used for sample size calculation was as follows:$$ N=\left[\left(1/{q}_1+1/{q}_2\right)\times {\left({Z}_{\alpha }+{Z}_{\beta}\right)}^2\right]/\left[{\left(E/S\right)}^2\right], $$

where *N* = sample size,

*q*_1_ = proportion of subjects in the treatment group (0.5),

*q*_2_ = proportion of subjects in the placebo group (0.5),

*Z*_*α*_ = critical value of the normal distribution at *α* (*α* = 0.05 and critical value = 1.96),

*Z*_*β*_ = critical value of the normal distribution at *β* (*β* = 0.2 and critical value = 0.84),

*E* = effect size (0.5% difference in HbA1c between the two groups) and

*S* = standard deviation of HbA1c in the population (in the absence of previous published studies on pre-diabetes in Sri Lanka that reported HbA1c values, this was assumed to be 0.82%, based on previous research conducted among patients with diabetes in Sri Lanka) [23].

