#### Suspension criteria

Subject’s demand to discontinue the study.Serious adverse events or unusual changes in clinical test results.Principal investigator’s decision to terminate the study (low rates of compliance, complications or unable to sustain the study for various reasons).

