### Outcomes

#### Primary outcome index

The primary outcome will be defined as the change in glycemic control measured by HbA1c from baseline.

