#### Study schedule

Fasting blood glucose, 2-h OGTT blood glucose, serum insulin, the liver profile (AST, ALT, PT/INR) and the renal profile (blood urea and serum creatinine) will be measured at the 0,1, 3 and 6 months. In addition, the serum lipid profile (total cholesterol, triglycerides, LDL cholesterol, HDL cholesterol) and serum HbA_1_c would be measured at baseline, at 3 months and on completion of the study. The details of items which will be measured at every visit are described in Fig. 1.

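### The plan commits to single (mean or regression) imputation of missing values, the primary HbA1c change included, when rates are low, and leaves multiple imputation optional above 10% although 20% drop-out is planned for

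*Protocol article*

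**What the plan says.** The rule is in the protocol article, Statistical analysis. It opens "In the case of missing data values" and continues "we will apply mean imputation and regression imputation where rates are low, and consider multiple imputations where they exceed 10" percent. It is not limited to covariates or to secondary measures. Under Primary outcome index, "The primary outcome will be defined as the change in glycemic control measured by HbA1c from baseline", so the rule reaches the primary endpoint.

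The same section says "All analyses will follow intention-to-treat principles and a prespecified analysis plan". It gives as examples of sensitivity analyses "control for additional covariates; and bootstrapped *P* values for skewed outcomes". Groups are compared by t tests and by multiple regression on change in HbA1c, with significance at P < 0.05.

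Under Sample size, the number required "with a drop-out rate of 20% was 108 patients". The Study schedule has HbA1c measured at baseline and again "at 3 months and on completion of the study".

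**The concern.** A value filled in by a mean or a fitted regression line carries no new information, but a t test or regression run on the completed data counts it as a full observation. Two different errors can follow:

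- If the filled value respects treatment arm, the effect estimate is unbiased (when values are missing completely at random) but the standard error is too small. P values are then too low and confidence intervals too narrow.
- If the filled value ignores treatment arm, both arms are pulled toward a common value and the estimated difference shrinks.

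The text does not say whether the mean is overall or by arm, whether the imputation regression includes treatment, or whether a random residual is added. Above 10% it only considers multiple imputation and names no fallback, while the sample size allows for twice that rate. What is at stake is the P value, or the estimate and interval, for the primary comparison.

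**Working it through.** **Inputs from Sample size:** 55 per arm, two-sided α = 0.05 (1.96), power 80% (0.84), E = 0.5, S = 0.82, drop-out 20%. **Assumptions, not in the documents:** values missing completely at random and balanced by arm; baseline–outcome correlation 0.5, which matters only for regression imputation and for baseline-adjusted analysis.

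**1. The plan's own figure.** N = (1/0.5 + 1/0.5) × (1.96 + 0.84)² / (0.5/0.82)² = 4 × 7.84 / 0.3718 = 84.3. Rounded up to 43 per arm this is 86, and 86/0.8 = 107.5, so 108. The stated figure is reproduced, and 20% drop-out is built into it.

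**2. Arm-mean imputation, by formula.** With n_o of n values observed per arm, the reported standard error divided by the true one is √[((n_o − 1)/(n − 1)) × (n_o/n)]. The nominal cut-off of 1.96 then acts as 1.96 × ratio.

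- 50 of 55 observed (9% missing): √[(49/54)(50/55)] = 0.908; 1.96 × 0.908 = 1.78; type I error about 7.5%.
- 44 of 55 observed (20% missing): √[(43/54)(44/55)] = 0.798; 1.96 × 0.798 = 1.56; type I error about 11.8%.

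No assumed correlation enters these figures.

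**3. Imputation that ignores arm, by formula.** With equal missing fractions m in both arms, the expected difference is about 0.50 × (1 − m): 0.475 at 5%, 0.45 at 10%, 0.40 at 20%.

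**4. Simulation.** 6,000 trials per setting. The Monte Carlo standard error at a 5% rejection rate is √(0.05 × 0.95/6000) = 0.3 percentage points.

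| Method | Quantity | 5% missing | 10% missing | 20% missing |
|---|---|---|---|---|
| Complete cases, t test | Type I error | 4.8% | 5.4% | 4.6% |
| Arm mean, t test | Reported/true SE | 0.95 | 0.89 | 0.80 |
| Arm mean, t test | Type I error | 6.1% | 8.0% | 12.0% |
| Regression with treatment, baseline-adjusted analysis | Type I error | 5.8% | 7.9% | 12.0% |
| Regression with treatment, t test | Type I error | 5.6% | 7.3% | 9.7% |
| Overall mean, t test | Type I error | 4.8% | 5.4% | 4.7% |
| Overall mean, t test | Estimate of a true 0.50 | 0.47 | 0.45 | 0.40 |
| Regression without treatment, baseline-adjusted analysis | Estimate of a true 0.50 | 0.47 | 0.45 | 0.40 |

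Complete cases serve as the valid reference here because values are missing completely at random; they estimate 0.50 at every rate. The regression imputation simulated is deterministic. Adding a random residual would preserve the outcome variance but would still ignore imputation uncertainty. Multiple imputation was not simulated.

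**The case against.** The strongest reply is that the large figures lie outside what the plan commits to. Above 10% the text points to multiple imputation, so 12% type I error or dilution to 0.40 arises only if multiple imputation is considered and then not used. That stands: the 20% column is conditional. In the committed range the harm is modest.

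A second reply is that the article does not fix the variant, so it cannot be said flatly that the P value will be wrong. That also stands. The two harms are alternatives, and overall-mean imputation leaves type I error near 5%. But each deterministic variant simulated gives either an interval that is too narrow or a diluted estimate.

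A third reply is that a separate analysis plan may settle the matter. This has less force, because the article states a method, and a plan that follows it inherits the fault. It is right, however, that leaving out how the 3-month HbA1c is used, or how follow-up after suspension works, is no fault in an article.

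Two stronger readings are tempting and are not supported:

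- A reader might infer a conflict with the intention-to-treat statement. There is none: imputing keeps all randomised participants in the analysis. The weakness lies in the inference, not in who is analysed.
- A reader might infer from the Suspension criteria ("Serious adverse events or unusual changes in clinical test results") that missingness will depend on outcome. The section does not say that HbA1c measurement ends on suspension, and its mention of poor compliance sits within a decision to terminate the study. Outcome-dependent missingness is possible but not established, and it is not quantified here.

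**Conclusion.** The point holds as a stated method that should be corrected, not as a fatal flaw. Where the plan commits to single imputation, the cost is a type I error of about 6% (5% missing) to 7.5–8% (9–10% missing) instead of 5%, or a true 0.50 difference estimated as about 0.47 to 0.45. At the planned 20% drop-out the cost would be about 12%, or 0.40, but only if single imputation were retained, which the word chosen for multiple imputation allows.

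These figures assume 55 per arm and balanced missingness completely at random; the regression-imputation figures also assume a correlation of 0.5 and no added residual. Taking the committed range to be up to 10% is itself an inference, from low rates being set against rates above 10%.

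**What to change.** Replace the sentence on missing values. For outcomes, delete mean and single-regression imputation at any missing rate, and replace the optional wording with a firm commitment, for all randomised participants, to one of:

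- a likelihood-based repeated-measures model of the 3- and 6-month HbA1c, with treatment by visit, baseline HbA1c, age and sex; or
- multiple imputation whose model includes treatment arm, baseline HbA1c and 3-month HbA1c.

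Both rest on missingness being explained by the data in the model. A sensitivity analysis under missing-not-at-random assumptions would be a useful optional addition.

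The cost is a short text change. No extra patients or measurements are needed, since the 3-month HbA1c is already scheduled, and Trial status says that enrolment has not begun. Confidence intervals become wider than arm-mean imputation would report. At 10% missing, the complete-case standard error exceeds the arm-mean one by a factor of 0.1645/0.1479 = 1.11. That width is the correct one for complete data; using the 3-month values may recover some of it.

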### Adverse effect evaluation

All of the active ingredients are supplemented within the Recommended Daily Allowance (RDA) [25, 26]. Therefore, the type of adverse events expected are likely to be minor in nature. However, in the event of a probable adverse reaction the following precautions would ensure timely identification and management of patients:Reporting—mechanisms would be set up to ensure direct reporting of probable adverse events to investigators by patients (via telephone available 24 h on all days).During follow-up visits, probable adverse events would be noted by history and examination and investigated in detail. All adverse effects observed will be documented in the case report form (CRF).Any serious adverse event as defined in GCP guidelines will be reported to the National ADR monitoring center at the Department of Pharmacology, Faculty of Medicine, University of Colombo within 24 h, the Ethics Committee, Faculty of Medicine, University of Colombo and the Clinical Trials subcommittee of the Drug Regulatory Authority within 1 week.A Data Safety Monitoring Board (DSMB) identified by the investigators will evaluate all adverse events at regular intervals.Investigations—liver and renal functions would be assessed as detailed earlier.Management—in the event of an adverse reaction requiring in-hospital management, the facilities and expert management would be available at the Nawaloka Hospital PLC, Colombo, Sri Lanka.Termination of study—the complete clinical trial will be terminated prematurely if there is evidence that the safety of the trial participants can no longer be assured or new scientific information arises during course of the clinical trial regarding safety of the patients.

